### Blinding

It was impossible to blind either the treating doctors or patients in this trial. In order to ensure the quality of this research, the assessors will be blinded. The outcomes of patients will be measured and filled in paper Case Reports Froms (CRF) by special researchers who would not take part in the allocation and the treatment.

### Treatment

After eligible patients are admitted to the hospital, the investigator will collect the basic information of patients, sign the informed consent and identify the randomized assignment as soon as possible. For all the patients, best medical treatments followed the recommendation of 2010 ASA/AHA intracerebral hemorrhage guidelines and preoperational preparation will be conducted at the same time. The patients will receive the corresponding surgery based on the result of randomization. All the surgeries will be performed as soon as possible after the randomization.

#### Craniotomy

This group of patients will receive hematoma evacuation by craniotomy. Well-trained neurosurgeons will decide surgical approaches according to the result of neuronavigation. The hematomas will be evacuated as much as possible with the help of operation microscope following the principle of “no brain stretch, electrocoagulation with small power, and slight aspiration”. A “Rebleeding test” will be performed after hemostasis. For patients with hypertension, the blood pressure will be slowly elevated to the level before the anesthesia, and for other patients, a raise of 20 ~ 30 mmHg will be gained. The anesthetist will maintain this level of blood pressure for 10 minutes. Only if there is no new bleeding site, neurosurgeons can start to close.

#### Neuroendoscopic surgery

This group of patients will receive hematoma evacuation by endoscopic surgery. Neurosurgeons will decide surgical approaches according to the result of neuronavigation. The hematomas will be evacuated as much as possible with the help of angled endoscope, but the stiffly attached clot won’t be removed by force in order to prevent unnecessary damage, and the restricted intracavity operation will be the principle during the hematoma evacuation. “Rebleeding test” will be conducted before close.

#### Stereotactic aspiration

This group of patients will receive hematoma evacuation by stereotactic aspiration. The puncture site will be based on the result of neuronavigation aimed to avoid functional domains and blood vessels. After puncture needlepoint placed to the center of the hematoma, the needle will be fixed onto the skull. As much of the hematoma as possible will be aspirated. Urokinase will be injected through the puncture needle afterward. The dosage of urokinase is based on the volume of hematoma (10000–50000 U). CT scan will be performed immediately after the procedure.

### Data collection and follow-up

After patient enrollment, we will collect their basic data at neurological evaluation, functional status assessment and imaging for baseline information, and follow up data will be collected at the time of seven days, one month, three months and six months after surgery. The plan of data collection is showed in Table 1. All the data will be recorded in the CRF in time. The filled CRF will be sent to trial secretary expeditiously.

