### Outcomes

#### Primary outcome

The primary outcome of this study is the unfavorable outcome at 6 months. The unfavorable outcome includes death and dependency after randomization. The dependency will be defined by using the Glasgow Outcome Scales (GOS) at 6 months after randomization.

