#### Secondary outcomes

The secondary outcomes include: mortality at 30 days, and 6 months after surgery; neurological functional status of 6 months after surgery measured by GOS, Modified Rankin Scale (mRS), Barthe index (BI), and National Institutes of Health Stroke Scale (NIHSS) separately; complications include rebleeding, ischemic stroke, intracranial infection; days of hospitalization.

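### The primary outcome is timed from randomization, but the visits that supply it, and the mortality and functional secondary outcomes, are timed from surgery

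*Protocol article*

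**What the plan says.** All references are to the protocol article.

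- **Primary outcome.** "The unfavorable outcome includes death and dependency after randomization". The next sentence reads: "The dependency will be defined by using the Glasgow Outcome Scales (GOS) at 6 months after randomization". Both components start at randomization.
- **Data collection and follow-up.** "follow up data will be collected at the time of seven days, one month, three months and six months after surgery". Table 1 has one 6-month column, with no origin in its label, and lists GOS in it once.
- **Secondary outcomes.** "mortality at 30 days, and 6 months after surgery", and "neurological functional status of 6 months after surgery measured by GOS" together with mRS, Barthel index and NIHSS. The Design paragraph of the Abstract also dates mortality and functional status from surgery. The remaining secondary outcomes carry no origin: "complications include rebleeding, ischemic stroke, intracranial infection; days of hospitalization".
- **Treatment.** "All the surgeries will be performed as soon as possible after the randomization". No maximum interval is given.
- **Statistical analysis.** The analysis is by intention to treat, with the log-rank method for time-to-event outcomes.

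**The concern.** Surgery happens after randomization and may not happen at all. An outcome dated from surgery is undefined for a randomized patient without an operation, whereas intention to treat requires a value, or a stated rule, for every randomized patient. The same 6-month GOS also serves as a primary outcome on one clock and a secondary outcome on another, so the visit that collects it cannot be scheduled to satisfy both definitions exactly.

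The interval between the two clocks can contain events. Eligible patients have a GCS of 5 to 12, a haematoma of at least 30 ml and onset within 48 hours, and the Background cites a 30-day case fatality of 30% to 55%. Death, deterioration or withdrawal between allocation and operation is foreseeable. At stake are the 30-day and 6-month mortality comparisons and, to a lesser degree, completeness of the 6-month assessment in unoperated survivors.

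**Working it through.** **1. The time origins side by side**

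| Item | Stated origin | Section |
|---|---|---|
| Primary: death | Randomization | Primary outcome |
| Primary: GOS at 6 months | Randomization | Primary outcome |
| Visits at 7 days and 1, 3 and 6 months | Surgery | Data collection and follow-up |
| Mortality at 30 days and 6 months | Surgery | Secondary outcomes; Abstract |
| GOS, mRS, BI, NIHSS at 6 months | Surgery | Secondary outcomes; Abstract |
| Complications, days of hospitalization | None stated | Secondary outcomes |
| Planned post-operative CT scans | Operation | CT scan |

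**2. What follows for each kind of patient**

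- *Operated.* The clocks differ by the randomization-to-surgery interval, which is meant to be short. The effect on a 6-month assessment is small.
- *Died before surgery.* Counted as unfavorable in the primary outcome. For mortality after surgery there is no time zero, and the text does not say how the death is classified.
- *Alive, never operated on.* The primary definition fixes a GOS date, but the visit schedule gives none. The surgery-dated functional outcomes have no defined time point.

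**3. Does any stated figure depend on the origin?**

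Inputs from Sample size: rates 58%, 51% and 51%, two-sided 5%, power 80%, N = 2203, enlarged to 2448 (816 per arm). The plan's figure is reproduced by the overall chi-square test with 2 degrees of freedom and equal arms:

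- mean rate = (0.58 + 0.51 + 0.51)/3 = 0.5333
- noncentrality = (N/3) × Σ(p − mean)² / [mean × (1 − mean)] = (N/3) × 0.003267/0.2489
- the smallest N with power of at least 80% is 2203 (power 0.8001)
- 2203/0.9 = 2448 after rounding up, with power 0.843

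None of these inputs involves a time origin, so re-dating the outcomes leaves both totals unchanged.

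**4. Possible size, under assumed rates**

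The article gives no rate of unoperated patients. If 1% to 3% were never operated on, 2448 × 0.01 = 24 to 2448 × 0.03 = 73 patients would lack a time zero for the surgery-dated outcomes.

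Suppose two arms have the same true mortality *m*, and a share *f* of an arm dies before surgery. If those patients are dropped from numerator and denominator, observed mortality is (*m* − *f*)/(1 − *f*). Taking *m* from the 30% to 55% range in the Background:

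| Assumed *f*, arm A / arm B | *m* = 30% | *m* = 55% |
|---|---|---|
| 2% / 2% | no difference | no difference |
| 2% / 0% | 28.6% vs 30.0%: 1.4 points | 54.1% vs 55.0%: 0.9 points |

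If the patients stay in the denominator but are not counted as deaths, the 2% / 0% case gives the full 2 points. A spurious difference arises only if such deaths are left out *and* their frequency differs between arms.

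Loss of numbers is a minor matter by comparison. If 5% of every arm (816 × 0.95 = 775 remaining) had no primary outcome, the 2-df power would go from 0.843 to 0.822.

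**The case against.** The strongest reply is that this is loose wording with little consequence. Intention to treat is stated, the primary outcome is correctly dated, surgery is to follow promptly, and Table 1 and the Abstract's list of visits name no origin. Deaths cannot disappear: Data and safety monitoring defines death as an SAE, to be recorded in the CRF and notified to the DSMB within 24 hours. How unoperated patients are scheduled could be left to a fuller protocol or analysis plan.

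Much of this stands, and it rules out several stronger readings that a reader might infer:

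- *That unoperated patients fall out of the trial.* No sentence excludes them, and deaths before surgery count in the primary outcome.
- *That the primary outcome is missing for them.* The dead need no visit, and for survivors the primary definition itself supplies a date. What is unclear is the visit.
- *That the clock depends on the arm and favors the one with the longer wait.* One timing rule covers all three arms, all three use neuronavigation, and no differential delay is reported. Neither the presence nor the direction of a bias can be read from the document.
- *That all secondary outcomes run from surgery.* Complications and days of hospitalization have no stated origin.

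What the reply does not remove is the contradiction. The article states two origins for the same 6-month GOS and a surgery origin for mortality under an intention-to-treat analysis. That is a stated rule in conflict with another, not a detail left out for brevity. Recording a death as an SAE does not settle whether it counts in mortality after surgery.

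**Conclusion.** The point holds as an inconsistency of time origin that should be corrected. It does not invalidate the primary outcome. For operated patients the discrepancy is only the randomization-to-surgery interval. For unoperated patients, the surgery-dated mortality and functional outcomes have no time zero, and survivors have no consistently defined visit date.

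The document does not allow any resulting bias to be quantified in amount or direction. The 0.9 to 2 points shown above rest on three assumptions: 2% versus 0% dying before surgery, equal true mortality of 30% to 55%, and an analysis that fails to count those deaths. The shift would concern the secondary mortality comparison. It should not be set against the 7-point difference (58% to 51%) planned for the primary outcome, which keeps those deaths.

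**What to change.** In Data collection and follow-up, date the 7-day, 1-month, 3-month and 6-month visits from randomization. In Secondary outcomes and the Design paragraph of the Abstract, date 30-day and 6-month mortality and 6-month functional status from randomization. State that this applies to all randomized patients, operated or not. Keep post-operative timing only for the planned CT scans and procedure-linked complications.

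The cost is protocol and CRF wording. Visit dates shift by the randomization-to-surgery interval. The sample size stays at 2203, enlarged to 2448.

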**Table 1 Tab1:** **Data collection program**

	**Baseline**	**7 days**	**1 months**	**3 months**	**6 months**
**GCS**	√	√			
**GOS**			√	√	√
**NIHSS**	√	√	√	√	√
**mRS**			√	√	√
**BI**			√	√	√
**Laboratory examination**	√	√	√	√	√
**Imaging**	√	√	√		

GCS: Glasgow Coma Scale; GOS: Glasgow Outcome Scale; NIHSS: National Institute of Health stroke scale; mRS: modified Rankin Scale; BI: Barthel Index.

### Outcomes

#### Primary outcome

The primary outcome of this study is the unfavorable outcome at 6 months. The unfavorable outcome includes death and dependency after randomization. The dependency will be defined by using the Glasgow Outcome Scales (GOS) at 6 months after randomization.

#### Secondary outcomes

The secondary outcomes include: mortality at 30 days, and 6 months after surgery; neurological functional status of 6 months after surgery measured by GOS, Modified Rankin Scale (mRS), Barthe index (BI), and National Institutes of Health Stroke Scale (NIHSS) separately; complications include rebleeding, ischemic stroke, intracranial infection; days of hospitalization.

### CT scan

Pre-planned CT scan is at admitting, 1 day, 3 days, and 7 days after operation. Unplanned CT scan is decided by the doctors if necessary. The volume of hematoma is calculated by the formula A*B*C/2. Rebeeding is defined as the postoperative hematoma volume was either greater than which before the operation or there was a less than 5-ml difference between the pre- and postoperative hematoma volume measurement.

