The treatment of sICH is still controversial among neurosurgeons and neurologists. The focus of debate is whether evacuation of hematoma would be able to improve the prognosis of patients. Previous studies showed that the removal of hematoma might reduce nervous tissue damage, possibly by relieving local ischemia and removing noxious chemicals [6-8]. Several studies aiming to explore the efficacy of surgery for patients with sICH have been carried out but showed different results. In 1961, Mickissock and colleagues published the first prospective randomized controlled trial. Their results showed that patients treated surgically had worse outcome than the patients in the conservative group [9]. Another influential study is the STICH series trials, which concluded that there was no overall benefit of early surgery for patients with supratentorial sICH compared with conservative treatment [10,11]. Some researchers attributed this to additional surgical traumatization. In order to reduce surgical traumatization, some minimally invasive techniques have been used in hematoma evacuation. These minimally invasive techniques include stereotactic aspiration and neuroendoscope assisted surgery. The stereotactic aspiration guided by CT was successfully applied for hematoma evacuation by Backlund and collogues at 1978, and this minimally invasive surgery was further improved by some scholars [12]. It was reported that the stereotactic aspiration combined with fibrinolytic drugs could be more effective in hematoma evacuation than aspiration alone [13]. Another category of minimally invasive technique is neuroendoscope. Auer et al. reported that neuroendoscope could be applied to hematoma evacuation, but a subsequent randomized controlled trial showed that the outcome of surgical patients with putaminal or thalamic hemorrhage was not better than medical treatment [14,15]. Recently, a lot of studies exploring the efficacy of minimally invasive surgery (MIS) compared with conservative craniotomy or medical treatment were carried out, but none of them provided sufficient evidence regarding the choice of treatment [16-20]. A further meta-analysis showed that patients with supratentorial intracerebral hemorrhage might benefit more from MIS than other treatment options [21]. Though MIS seems less invasive than the traditional craniotomy, it was reported that the incidence of some complications (e.g. rebleeding and infection) was higher than craniotomy. In addition, with assistance of neuronavigation and operative microscope, hematoma evacuation by craniotomy could also be minimally invasive [22,23]. Until now, there is no randomized controlled trial comparing the efficacy of neuroendoscopy, stereotactic aspiration and craniotomy in patients with spontaneous intracerebral hemorrhage except a small-scale trial by Cho and colleges. Thus, a large-scale clinical trial is necessary to provide robust evidence for clinical practice by assessing the safety and efficacy of different surgical methods including neuroendoscopy, CT-stereotactic aspiration and neuronavigation-assisted craniotomy for sICH. Here we designed a randomized, assessor-blinded, parallel-group, controlled, multi-center clinical study termed minimally invasive surgery treatment for patients with spontaneous supratentorial intracerebral hemorrhage (MISTICH).

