### Patient population

#### Inclusion criteria

Age between 15 and 75 years;Diagnosed with acute spontaneous supratentotial intracranial hemorrhage (Meets U.S. adults spontaneous intracerebral hemorrhage treatment guidelines (2010) diagnostic criteria)Within 48 hours post ictus;With Glasgow Coma Scale (GCS) between 5 and 12;CT scan showed hematoma volume is 30 ml or above;Agree to participate in this clinic trial and sign the informed consent.

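### Rebleeding is measured against the preoperative clot, so the rule captures only near-complete refilling, also flags near-failed evacuation, and can distort the comparison between arms

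*Protocol article*

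**What the plan says.** Under CT scan, the article states: "Rebeeding is defined as the postoperative hematoma volume was either greater than which before the operation or there was a less than 5-ml difference", and completes the second limb as a "less than 5-ml difference between the pre- and postoperative hematoma volume measurement". No other definition of rebleeding appears. The same section sets the schedule for all arms: "Pre-planned CT scan is at admitting, 1 day, 3 days, and 7 days after operation". It does not say which postoperative scan supplies the postoperative volume.

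Eligibility requires that the "CT scan showed hematoma volume is 30 ml or above". Secondary outcomes list the event by name: "complications include rebleeding, ischemic stroke, intracranial infection". Study objective makes safety of the techniques the secondary objective, and Statistical analysis assigns categorical secondary outcomes to the chi-square test. Background reports that with minimally invasive surgery "the incidence of some complications (e.g. rebleeding and infection) was higher than craniotomy".

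The Treatment subsections tell surgeons in all three arms to remove as much clot as they can. The endoscopy arm adds that firmly adherent clot is not forced out. In the aspiration arm, "Urokinase will be injected through the puncture needle afterward", and for that arm alone "CT scan will be performed immediately after the procedure".

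**The concern.** A rebleeding outcome should detect blood that appears after the operation. This needs a postoperative reference volume, so that later growth can be seen. The article uses the preoperative volume instead. Once most of a clot has been removed, a substantial new bleed can still leave the total well below the starting volume, and the rule then records no event. Conversely, a patient from whom almost nothing was removed is recorded as having rebled although no new bleeding occurred.

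Both errors depend on how much clot was evacuated, which is a consequence of the randomized technique. If evacuation differs between arms, the sensitivity of the rebleeding measure differs too, and a larger sample does not cure that. At stake is whether the trial can answer the safety question that its Background raises. A difference between arms, or the absence of one, could reflect completeness of evacuation and not bleeding.

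This is a stated rule that gives wrong classifications when followed exactly. It is not a detail left to an analysis plan, and a plan that applied it faithfully would inherit the error.

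**Working it through.** The article gives no rebleeding rate, power or evacuation fraction, so there is no figure of its own to reproduce here. The check is arithmetic on the definition.

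**Inputs**
- V, preoperative volume: at least 30 ml (Inclusion criteria). Values of 60 and 100 ml are illustrative assumptions.
- 5 ml margin (CT scan).
- e, fraction evacuated: not given. I assume 50%, 70%, 90% and 100% to show the range.
- B, volume of new bleeding after surgery.

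**Step 1: the rule in one line.** An event is recorded if post > V, or if the two volumes differ by less than 5 ml. Together these reduce to post > V − 5.

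**Step 2: bleed needed to be counted.** Residual clot is (1 − e)V, so post = (1 − e)V + B. The condition becomes B > eV − 5.

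| Evacuated | V = 30 ml | V = 60 ml | V = 100 ml |
|---|---|---|---|
| 50% | 15 − 5 = 10 ml | 30 − 5 = 25 ml | 50 − 5 = 45 ml |
| 70% | 21 − 5 = 16 ml | 42 − 5 = 37 ml | 70 − 5 = 65 ml |
| 90% | 27 − 5 = 22 ml | 54 − 5 = 49 ml | 90 − 5 = 85 ml |
| 100% | 30 − 5 = 25 ml | 60 − 5 = 55 ml | 100 − 5 = 95 ml |

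New bleeding up to and including the tabulated volume is not counted. Within each column the threshold rises with completeness of evacuation.

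**Step 3: flagged with no new bleeding.** Put B = 0. The patient is flagged if eV < 5 ml. That is less than 5/30 = 16.7% of a 30 ml clot, 5/60 = 8.3% of 60 ml, or 5/100 = 5% of 100 ml.

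**Step 4: single patients**
- 60 ml before surgery, 6 ml on day 1, 40 ml on day 3: new bleeding is 40 − 6 = 34 ml, but the difference from the preoperative volume is 60 − 40 = 20 ml. Not counted.
- 34 ml before, 30 ml after, no new bleeding: the difference is 4 ml. Counted.

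**Step 5: scan timing.** The common postoperative scans are days 1, 3 and 7. The first example shows that this schedule can reveal growth between scans, but the definition makes no use of it.

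**The case against.** A reader might infer that the rule works specifically against aspiration: residual clot is counted as rebleeding there, an extra early scan gives that arm one more chance to be flagged, and the arms that evacuate more have their true rebleeds hidden. The documents do not support this:
- All three arms carry the same instruction to remove as much as possible. The only residual deliberately left is adherent clot in the endoscopy arm. Urokinase follows aspiration, but nothing says that clot is left for it.
- No evacuation rates are given for any arm.
- The definition follows directly on the common schedule, and nothing says that the immediate aspiration CT is scored for rebleeding. The supportable point is narrower: the definition does not name the scan that counts.

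Two further limits stand. Not every rebleed is missed, because one that refills to within 5 ml of the starting volume is counted. Not every incomplete evacuation is flagged, because only net removal under 5 ml is, and that is close to complete failure.

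The outcome's weight also matters. Rebleeding is one of three named complications among the secondary outcomes. It does not enter the primary outcome, the sample size, or the article's SAE definition (death and persistent vegetative state), which the stopping rule uses. Serious consequences of a missed rebleed can still show in mortality and the functional scales.

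Finally, taking day 1 as the only reference would have a fault of its own. Bleeding before that scan would be absorbed into the reference, then found only through reoperation or unplanned CT ordered by doctors who know the allocation. That objection is sound and shapes the fix. None of these points repairs the definition itself.

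**Conclusion.** The concern holds in this form. The stated rule detects near-complete refilling of the cavity and near-failed evacuation; it does not detect rebleeding as such. After 90% evacuation (assumed), new bleeding must exceed 22 ml from a 30 ml clot, or 49 ml from a 60 ml clot, to be counted. Without any new bleeding, a patient is flagged when less than 5 ml was removed.

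The rule itself, the 30 ml entry minimum and the 5 ml margin come from the article; the evacuation fractions and the larger volumes are assumptions. Because the threshold depends on completeness of evacuation, the comparison between arms can be distorted if techniques differ in that respect. That they do differ is plausible but not documented, and the direction and size of any distortion cannot be stated. This should be corrected before the outcome is analysed, but it does not threaten the primary result.

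**What to change.** 1. Define rebleeding as growth in hematoma volume between postoperative scans on the schedule common to all arms, from day 1 to day 3 or day 7, by a pre-specified amount, or as new hemorrhage shown on CT or at reoperation. The 5 ml margin already in the CT scan section is a candidate for the growth threshold. The article does not justify it for this use, so the sponsor should confirm it.
2. Keep the present comparison with the preoperative volume as a separate item, applied to the day-1 scan in every arm and labelled as failed evacuation or near-complete refilling. Large rebleeds before day 1 then stay visible.
3. State that the immediate CT in the aspiration arm is not used in the between-arm comparison. The scan itself is untouched.
4. Report events found on planned scans separately from those found on unplanned scans.

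The cost is wording in the protocol and CRF. The scans are already planned, and patient management does not change. The remaining weakness is that a bleed before the day-1 scan that does not bring the volume to within 5 ml of the preoperative value is seen only through unplanned CT or reoperation. Unblinded doctors decide on these, so ascertainment could differ between arms. Item 4 exposes that weakness but does not remove it.

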**Flow diagram of the MISTICH study.**

### Study objective

The primary objective is to evaluate different minimally invasive techniques including neuronavigation assist craniotomy, neuroendoscopy, and CT-stereotactic aspiration on their unfavorable outcomes at 6 months in patients with spontaneous intracerebral hemorrhage. The secondary objective is to investigate the safety of different minimally invasive techniques. Another objective is to evaluate the separate effects of treatment on death and dependency through physical function, complications, and days of hospitalization.

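### The rebleeding definition does not say which postoperative CT counts, and only the stereotactic aspiration arm has an immediate CT, so this safety outcome can be ascertained unequally between arms

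*Protocol article*

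**What the plan says.** The CT scan section of the protocol article gives the schedule for all patients: "Pre-planned CT scan is at admitting, 1 day, 3 days, and 7 days after operation". It adds: "Unplanned CT scan is decided by the doctors if necessary". The same paragraph then gives the outcome rule, which has two limbs. The first reads: "Rebeeding is defined as the postoperative hematoma volume was either greater than which before the operation". The second limb is met when "there was a less than 5-ml difference between the pre- and postoperative hematoma volume measurement". Either limb is enough, and no scan, day or window is attached to the postoperative measurement.

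The Stereotactic aspiration section describes needle aspiration and then says: "Urokinase will be injected through the puncture needle afterward". It ends: "CT scan will be performed immediately after the procedure". The Craniotomy and Neuroendoscopic surgery sections have an intraoperative rebleeding test before closure and order no immediate CT.

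Rebleeding is one of the complications listed under Secondary outcomes. Under Statistical analysis, categorical secondary outcomes are compared by chi-square test, with P≤0.05 taken as significant. The Study objective section says: "The secondary objective is to investigate the safety of different minimally invasive techniques".

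**The concern.** A comparison of complication rates is fair only if each arm has the same opportunity to be found positive. Read literally, the rule covers any CT taken after the operation. A CT taken straight after aspiration is such a scan, and no other arm has a planned counterpart.

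The extra scan is also the one most open to misclassification. Aspiration relies partly on urokinase dissolving clot after the needle has done its work. A CT at the end of the procedure sees the hematoma before that has happened. If less than 5 ml has been removed by then, the second limb is met with no new bleeding at all, and the same patient may no longer meet it on day 1.

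The comparison at stake is a named safety outcome with an expected direction. The Background says of minimally invasive surgery that "it was reported that the incidence of some complications (e.g. rebleeding and infection) was higher than craniotomy". An excess in the aspiration arm produced by the additional scan would point the same way and could not be told from a true effect.

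**Working it through.** **Step 1: planned postoperative CTs in the first week, by arm**

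| Arm | Immediate | Day 1 | Day 3 | Day 7 | Total |
|---|---|---|---|---|---|
| Craniotomy | none ordered | yes | yes | yes | 3 |
| Neuroendoscopy | none ordered | yes | yes | yes | 3 |
| Stereotactic aspiration | yes | yes | yes | yes | 4 |

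Table 1 also ticks imaging at 1 month, modality not given, for every arm. That does not change the difference of one.

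**Step 2: what each possible reading implies**

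- *Any postoperative scan qualifies.* Aspiration has one additional, early chance to meet the rule. The excess consists only of patients who meet it on the immediate CT and on none of the common CTs. The bias is against aspiration, or zero if there are no such patients.
- *Only the first postoperative scan counts.* The index scan is the immediate CT in aspiration and the day 1 CT elsewhere. Clot not yet lysed pushes the aspiration rate up. Bleeding between the immediate CT and day 1 is missed in that arm only, which pushes it down. The net direction is uncertain.
- *Only the day 1, 3 and 7 CTs count.* The schedule is the same in all arms and there is no imbalance.

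**Step 3: how many patients would matter under the any-scan reading**

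The article gives no rebleeding rate and no figure to reproduce. The one input from the document is n = 2448/3 = 816 per arm (Sample size section). The event rates below are assumptions.

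Each immediate-only positive adds 1/816 = 0.12 percentage points to the aspiration rate. For k events in aspiration and c in one other arm, the uncorrected chi-square is

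X² = 2n(k − c)² / [(k + c)(2n − k − c)], with 2n = 1632.

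Start from equal counts c and find the smallest k giving P≤0.05:

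| Assumed rate | c | k | Extra patients | X² | P |
|---|---|---|---|---|---|
| 3% | 24 | 40 | 16 (2.0% of arm) | 1632×16²/(64×1568) = 4.16 | 0.041 |
| 5% | 41 | 61 | 20 (2.5%) | 1632×20²/(102×1530) = 4.18 | 0.041 |
| 10% | 82 | 108 | 26 (3.2%) | 1632×26²/(190×1442) = 4.03 | 0.045 |

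A single three-arm chi-square needs 16, 21 or 27 extra patients.

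Smaller excesses raise the chance of a false difference more modestly. Let the common-scan risk be R in both arms and the aspiration risk R + e, so that the spurious risk ratio is (R + e)/R:

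| e | About how many patients | Risk ratio at R = 3%, 5%, 10% | Chance of P≤0.05 against one other arm |
|---|---|---|---|
| 0 | 0 | 1.00, 1.00, 1.00 | 5%, 5%, 5% |
| 0.5% | 4 | 1.17, 1.10, 1.05 | 9%, 7%, 6% |
| 1% | 8 | 1.33, 1.20, 1.10 | 19%, 14%, 10% |

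A handful of such patients matters little. Around 2% to 3% of the arm would be enough to create a significant difference from equal counts.

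**The case against.** The strongest reply is that the CT scan section reads as one unit: it lists the planned scans and then defines rebleeding. The immediate CT sits in the treatment description as the last step of the procedure and is not on that list. On the natural reading, outcome volumes come from the listed scans and the imbalance is zero. Which scan feeds a secondary complication may also be settled in a fuller protocol that is not shown.

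Much of this stands, and it is why the point is conditional. It does not dispose of it. The definition is not limited to the listed scans, and the paragraph mentions unplanned CTs just before giving it. The article itself prints both the open definition and the arm-specific scan, so the issue is how these two statements combine, not a detail left out for length.

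A second reply is that the affected group is narrow. A hematoma of at least 30 ml must shrink by less than 5 ml, or grow, although maximal aspiration was attempted, and must then fail the rule on days 1, 3 and 7. A true early rebleed would often still be visible on day 1. This stands too: the number of such patients is unknown and may be small.

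A reader might infer that the rebleeding outcome is biased against aspiration, or that it must be if the immediate CT counts at all. The document supports neither. Nothing says that the immediate CT counts, and under a first-scan rule the direction is uncertain.

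**Conclusion.** The rebleeding rule leaves open which scan decides, and imaging differs between arms at exactly the point where this matters. As written, the rule admits unequal ascertainment of a secondary safety outcome.

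The bias is against aspiration if any postoperative scan can qualify and some patients are positive on the immediate CT alone. Its direction is uncertain if only the first scan counts, and it is absent if only the day 1, 3 and 7 CTs count. Its size cannot be derived from the document. The thresholds of 16, 20 and 26 patients rest on assumed equal rates of 3%, 5% and 10% and show only what would be needed. The primary outcome and the sample size are not affected. The point is worth correcting because the correction is simple, but it does not threaten the trial's main conclusion.

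**What to change.** In the CT scan section, state that the between-arm comparison of rebleeding uses the day 1, 3 and 7 CTs in all three arms, and that the immediate CT after aspiration does not count toward it.

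Report rebleeding seen on the immediate CT or on unplanned CTs separately by arm, including events that lead to re-operation or death before day 1. Add a sensitivity analysis that counts all scans. Note beside both that detection of these events is unequal: only aspiration has a routine immediate CT, and unplanned CTs are ordered by doctors who know the allocation. For the same reason, early events found on the immediate CT should not be let back into the main comparison because they were re-evacuated; that would restore the unequal trigger.

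This is a text change and needs no extra scans. The cost is that a few early events treated before day 1 move from the main comparison to the sensitivity analysis. The change does not alter the under-5-ml limb, which can still label incomplete evacuation as rebleeding on the common scans, but then on the same schedule in every arm.
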